### Aims and study hypotheses

Our primary aim is to test the immediate effect of the intervention at 4-months on symptom severity (PHQ-9 severity score) in African American older adults (primary trial outcome; between group comparison). Our hypothesis is that participants in the initial treatment group will report fewer depressive symptoms in comparison to control group participants receiving usual care. We also seek to test the maintenance effect of the intervention at 8-months on depression (within group comparison). Our hypothesis is that participants in the initial treatment group will maintain reduced symptom presentation from 4 to 8 months and the wait-list control group will show similar reductions in depressive symptoms as the initial treatment group (within group comparison).

A secondary aim is to evaluate whether BTB has immediate (4 months) and long-term (8 months) effects on quality of life indicators, functional difficulty, anxiety, and depression education and behavioral activation levels. We expect that the initial treatment group will show improvements in these areas relative to the wait-list control group, that improvements will be maintained at 8 months and that the wait-list control group will demonstrate similar improvements at 8 months following their receipt of the intervention.

Several exploratory aims are also proposed. We will evaluate the mechanism of action, or pathways, by which treatment gains are obtained. Given that behavioral activation represents conceptually the key active ingredient of the proposed intervention, we plan to evaluate its mediational effect. We will also evaluate whether the intervention has a differential treatment effect based on a study participant's gender, age, and living arrangement (alone or with others). Given that previous research suggests that participant characteristics may moderate depressive symptoms and treatment outcomes, these exploratory analyses will provide insight as to whether this particular treatment benefits some groups more than others.

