### Wait-list control group

The control group does not receive any study-related contact following the baseline interview. After completion of the 4-month reassessment, participants in this group receive the entire BTB intervention as delivered to the initial treatment group.

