As to our second aim, we seek to evaluate whether participants in the initial treatment group maintain reduced symptom presentation from 4 to 8 months. We view retention as a one-sided concept such that any beneficial effect of the intervention at four months is improved or at least maintained at 8 months. Lack of retention is then considered a non-trivial loss of benefit. In the language of clinical treatment trials, this is a "clinical equivalence" or "non-inferiority" hypothesis. Thus, our analyses for our second aim will focus on estimating the amount of 4-month benefit that is retained at 8 months for the treatment group only. We will use confidence intervals in reporting results in order to understand how much loss of benefit is consistent with the data we obtain. Given that the main outcome measure, PHQ-9, has cut off points related to DSM IV depression conditions (e.g., dysthymia, major depression), we will be able to evaluate loss of benefit and retention of effect within the treatment group based on clinically relevant features.

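### Retention at 8 months is read from the treated arm's own course, which cannot separate retained treatment effect from natural recovery

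*Protocol article*

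**What the plan says.** The Protocol article declares the 8-month aim under Aims and study hypotheses: "We also seek to test the maintenance effect of the intervention at 8-months on depression (within group comparison"). The same section expects that "the wait-list control group will show similar reductions in depressive symptoms as the initial treatment group (within group comparison").

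The Analytic plan then treats retention as a one-sided matter. It states: "Lack of retention is then considered a non-trivial loss of benefit". It continues: "In the language of clinical treatment trials, this is a 'clinical equivalence' or 'non-inferiority' hypothesis". The quantity to be reported is "estimating the amount of 4-month benefit that is retained at 8 months for the treatment group only", and the inference is by estimation: "We will use confidence intervals in reporting results in order to understand how much loss of benefit is consistent with the data we obtain". PHQ-9 cut-off points are offered as an aid to interpretation, so that "we will be able to evaluate loss of benefit and retention of effect within the treatment group based on clinically relevant features".

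Two other statements matter. The 4-month benefit is defined in the Analytic plan as an ANCOVA-adjusted mean difference between the two randomised groups, with baseline value and recruitment source as covariates. The section on the wait-list control group says: "After completion of the 4-month reassessment, participants in this group receive the entire BTB intervention as delivered to the initial treatment group". No untreated group therefore exists at 8 months.

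**The concern.** The benefit and its retention are defined on different scales. At 4 months, benefit means treated minus untreated. From month 4 to month 8, retention means that the treated group's own score does not rise. The two agree only if untreated participants would have stayed level over those four months, and the document gives no ground for that.

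If untreated participants would have gone on improving, a flat treated arm has lost part of its advantage, yet the analysis as written would report that advantage as kept. The wait-list group's fall between months 4 and 8 has the same weakness: some of it might have occurred without BTB. Comparing that fall with the treated group's fall over months 0 to 4 adds a further difficulty. The treated fall follows entry on two PHQ-9 scores of at least 5, and so may contain regression to the mean. The wait-list fall starts from a 4-month score on which nobody was selected.

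At stake is what the trial may say about durability and about replication in the wait-list group. The 4-month primary comparison is not affected.

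**Working it through.** The document gives no margin, sample size or power specific to the maintenance aim, so there is no figure of the plan's own to reproduce here. The check asks how much loss a single-arm reading could hide, and what an 8-month comparison of the arms would measure.

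**Inputs from the Protocol article**
- Target effect: d = 0.40 (Analytic plan).
- SD of PHQ-9: 4.9, at the second screen (Table 3).
- Enrolled: 208 (Recruitment and enrollment outcomes). Planned attrition: 10% (Analytic plan).

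**Assumptions, not in the document**
- The SD of 4.9 also holds at 4 and 8 months.
- Arms are equal, and 10% attrition applies at 8 months: 208 x 0.9 / 2 = 93.6, taken as 93.5 per arm.
- Untreated improvement is g points per 4 months, the same in each period, with g = 0, 1 or 2.
- f is the fraction of the 4-month effect still present at 8 months in the initial group. c is the fraction of that effect which delayed BTB has produced in the wait-list group by month 8.
- Correlations between visits are 0.4 to 0.6.

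**Step 1. Target effect in points.** E = 0.40 x 4.9 = 1.96.

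**Step 2. What the single-arm analysis sees.** Relative to baseline, the treated mean is -(g + E) at 4 months and -(2g + fE) at 8 months. The 4-to-8-month change is therefore E(1 - f) - g, where positive means worse. Apparent retention, the 8-month fall over the 4-month fall, is (2g + fE)/(g + E).

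| g | f (true retention) | 4-to-8-month change | Apparent retention |
|---|---|---|---|
| 0 | 1 | 0.00 | 100% |
| 0 | 0.5 | 0.98 | 0.98/1.96 = 50% |
| 0 | 0 | 1.96 | 0% |
| 1 | 0.5 | 0.98 - 1 = -0.02 | 2.98/2.96 = 101% |
| 2 | 0 | 1.96 - 2 = -0.04 | 4.00/3.96 = 101% |

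With no drift the single-arm reading is right. With 1 point of drift, loss of half the effect is invisible; with 2 points, loss of all of it is.

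**Step 3. What the randomised 8-month contrast sees.** The wait-list mean at 8 months is -(2g + cE). The difference, initial minus wait-list, is E(c - f). The drift g cancels.
- If c = 1, the difference is E(1 - f), which is the loss of benefit.
- If f = c = 1, the difference is 0: full retention and full delayed response.
- If f = c = 0, the difference is also 0: no benefit left in either arm.

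A difference near zero therefore does not identify retention by itself.

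**Step 4. Precision (95% half-widths).**
- Between arms, ANCOVA, with r the baseline-to-8-month correlation: 1.96 x 4.9 x sqrt(1 - r²) x sqrt(2/93.5) = 1.29, 1.22 and 1.12 points for r = 0.4, 0.5 and 0.6.
- Within the treated arm, with r the 4-to-8-month correlation: 1.96 x 4.9 x sqrt(2(1 - r)/93.5) = 1.09, 0.99 and 0.89 points for the same values.

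The between-arm interval is somewhat wider. The within-arm interval is narrower, but as an estimate of lost effect it is off by g.

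**The case against.** The strongest defence is that the limit is inherent and disclosed. A wait-list design has no untreated group at 8 months; the article claims a true two-group comparison only at 4 months and labels the 8-month aim as within-group. It plans estimation with confidence intervals and states no pass/fail rule. The drift values of 1 and 2 points are assumptions, and with zero drift nothing is masked. All of this stands. It does not rescue the wording, because the quantity to be estimated is still called retained benefit, and a disclosed single-arm design does not make a single-arm change a treatment effect.

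A reader might be tempted to go further in four ways, none of which the document supports.

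- *The randomised 8-month contrast would answer the maintenance question.* It would not do so unconditionally. Controls have received the entire BTB by then, so it compares early with delayed treatment. The assumption it needs, that delayed BTB works as well, is close to the aim's own hypothesis about the wait-list group.
- *The contrast is wholly unused.* The exploratory mediation regressions, including PHQ-9 on group assignment, are to be repeated with 8-month values. It is unused only for the maintenance aim.
- *The missing non-inferiority margin is itself the defect, and 1 point would repair it.* A margin for a non-primary aim is detail that an article may leave to the full plan. Nothing in the document supports 1 point, and with a half-width of 1.1 to 1.3 points even an observed difference of zero would not exclude a 1-point loss.
- *Testing the wait-list 4-to-8-month change against that group's own untreated 0-to-4-month change would settle replication.* The reference period may contain the regression to the mean that follows selection at entry, and the comparison is confounded with time.

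**Conclusion.** The point holds in a limited form. Followed as written, the second aim can report full retention when half of a 1.96-point effect has gone (assumed untreated improvement of 1 point between months 4 and 8) or when all of it has gone (assumed 2 points). The sizes rest on a constant SD of 4.9 and on drift values that the document does not give. Loss of half is not fanciful: the Analytic plan cites one trial whose effect fell from .70 at 6 months to .35 at 12, although another rose from .40 to .60.

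The fault lies in interpreting a single-arm course as retained treatment effect. It bears on the durability and wait-list claims only. Analysis cannot fully repair it, because no untreated group remains at 8 months; it can be described honestly and partly informed by the randomised arms.

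**What to change.** 1. Report the initial group's 4-to-8-month PHQ-9 change with its confidence interval as an uncontrolled course of symptom level. Do not call it retained treatment effect or draw a non-inferiority conclusion from it.
2. Treat the wait-list group's 4-to-8-month change in the same way.
3. Add to the maintenance aim an ANCOVA of 8-month PHQ-9 by randomised arm, with baseline PHQ-9 and recruitment source as covariates and all randomised participants in their assigned arm, labelled as early versus delayed BTB. State beside it that it measures loss of benefit only if BTB started at month 4 works as well as at month 0, and that a difference near zero does not by itself prove retention.
4. If the non-inferiority label is kept, fix a margin with its justification and confidence level before the 8-month data are analysed. The document gives no basis for any particular value.

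The cost is a change of wording and one further model. The 8-month interviews are already planned for everyone, so no new data are needed. The price is a somewhat wider interval (half-width about 1.1 to 1.3 points, against 0.9 to 1.1 within the arm) and a weaker claim about durability.

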For exploratory aims, we seek to evaluate the mediational role of behavioral activation. We will use separate regressions in which the first regression will evaluate the relationship between 4 month values of the behavioral activation scale (the mediator) and symptom severity as measured by the PHQ-9 at 4 months. The second regression will evaluate the relationship between group assignment (the independent predictor variable) and symptom severity at 4-months (PHQ-9, the criterion). The third regression will evaluate the relationship of treatment assignment (predictor) to PHQ-9 severity scores (criterion) after entering behavioral activation values (mediator). To evaluate the strength of the mediation effects, we will compute the ratio of the unstandardized betas for treatment assignment (beta from regression III divided by beta from regression II) with values less than 1.00 indicating potential mediation. We will repeat these analyses using 8-month values of the PHQ-9. Another exploratory aim is to evaluate whether the intervention has a differential treatment effect based on a study participant's gender, age, or living arrangement (alone/with others), factors which have been shown to be differentially related to depression. To evaluate differential treatment effects at 4-months, we will use a similar analytic strategy as for the main effect model. ANCOVAs will be used in which the covariates will be the baseline value and specific participant characteristic (e.g., male/female; live with other or alone; age 60-64 versus 75+). We will then add an interaction term of group assignment by participant characteristic.

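### The cut-off of 1.00 for the mediation ratio is crossed in about half of trials with no mediation, so it cannot indicate even potential mediation by behavioral activation

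*Protocol article*

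**What the plan says.** The aims section regards behavioral activation as the main active component of BTB and says, as an exploratory aim, "we plan to evaluate its mediational effect". The Analytic plan sets out three regressions:

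- **I.** The "first regression will evaluate the relationship between 4 month values of the behavioral activation scale (the mediator) and symptom severity". Treatment group is not mentioned in this model.
- **II.** "The second regression will evaluate the relationship between group assignment (the independent predictor variable) and symptom severity at 4-months". Its coefficient is the total effect.
- **III.** PHQ-9 on treatment group again, with activation already entered. Its treatment coefficient is the direct effect.

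The criterion is "beta from regression III divided by beta from regression II) with values less than 1.00 indicating potential mediation". It applies to the point estimate, and the text does not make it conditional on any other result. The plan then adds: "We will repeat these analyses using 8-month values of the PHQ-9".

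The group effect on activation is planned elsewhere. The secondary aim covers "functional difficulty, anxiety, and depression education and behavioral activation levels" at 4 and 8 months, and Table 1 lists the activation scale as a secondary outcome. The mediation paragraph does not refer to that result.

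**The concern.** A cut-off is useful only if it is crossed more often when the phenomenon is present than when it is absent, and seldom when it is absent. Here the cut-off is the value that the ratio takes when there is no mediation. Sampling error alone then puts the estimate below it in roughly every second trial.

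The article says its exploratory analyses should help refine hypotheses and the intervention, and about 6 or 7 of up to 10 sessions are given to behavioral activation. A ratio below 1.00 could be taken as support for that emphasis when it says almost nothing about it.

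**Working it through.** **Plan's own figure.** The article gives no error rate for the mediation rule, so there is none to reproduce. From the Analytic plan I take n = 172 evaluable participants and a total effect of 0.40 SD. Whether 172 delivers the stated power is a separate matter and does not affect this point.

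**Assumptions.** The scales are standardised and allocation is 1:1. Path sizes a and b are assumed, since the article gives none.

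**Step 1: what the ratio measures.** Let c be the treatment coefficient in regression II and c' that in regression III. For least squares on the same participants and covariates, c = c' + ab, so

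ratio = c'/c = 1 - ab/c.

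The ratio is below 1.00 exactly when the estimated ab has the same sign as the estimated c.

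- No mediation (ab = 0, c = -0.40): true ratio = 1 - 0/(-0.40) = 1.00.
- Mediation with a = 0.4, b = -0.4, c' = -0.24: ab = -0.16, c = -0.24 - 0.16 = -0.40, true ratio = 1 - 0.16/0.40 = 0.60.

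**Step 2: why about one half.** The standard error of c is about 2/√172 = 0.15 SD, so a true effect of 0.40 lies about 2.6 standard errors from zero and the estimated c almost always has the right sign. Whether the ratio is below 1.00 then depends on the sign of the estimated ab. If a = 0 or b = 0, that sign is close to a coin toss. More participants narrow the spread around 1.00 but do not move its centre.

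**Step 3: simulated rates with no mediation, c = -0.40.**

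| Case | n | Ratio < 1.00 |
|---|---|---|
| a = 0, b = -0.5 | 172 | 50.5% |
| a = 0, b = -0.3 | 172 | 50.0% |
| a = 0.4, b = 0 | 172 | 49.9% |
| a = 0, b = 0 | 172 | 50.4% |
| a = 0, b = -0.5 | 208 | 50.6% |
| a = 0.4, b = 0 | 208 | 49.8% |

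Independent runs with b = -0.4 in place of -0.5 gave 49-51%. The ratio can also sit well away from 1.00 by chance: with a = 0, b = -0.5, n = 172, its 5th and 95th percentiles are 0.72 and 1.58.

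**Step 4: if BTB has no effect at all (a = 0, c = 0).** The estimates of ab and c then share noise, with correlation about |b| on these scales. The chance of equal signs is 1/2 + arcsin(|b|)/π.

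- b = -0.4: 0.5 + 0.412/3.142 = 63%.
- b = -0.5: 0.5 + 0.524/3.142 = 67% (simulated: 66%).

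This bears on the 8-month repeat. By then "participants in this group receive the entire BTB intervention", and the plan itself expects the arms to show similar reductions, so c may be near zero.

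**Step 5: would the other planned pieces rescue the rule?**

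- Requiring regressions I and II to be significant: among trials that pass (about 75%), the ratio is below 1.00 in 59% (a = 0, b = -0.5).
- Requiring only a significant group effect on activation: 37% of trials still signal when a = 0.4 and b = 0.

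**Step 6: the alternative.** At n = 172, a bootstrap 95% interval for ab excludes zero in about 1-8% of no-mediation trials. With a = 0.4, b = -0.4 it detects mediation in about 73%. A joint significance test of both paths detects 74%, and the bare ratio is below 1.00 in 99%.

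**Step 7: limit of the alternative.** With a = 0.4, b = 0 and an assumed unmeasured common cause of activation and PHQ-9 (loading 0.5), the bare ratio signals in 99% of trials and the joint test still signals in 68%.

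**The case against.** The strongest reply is that the ratio is an effect measure and not a test. It is introduced to gauge the strength of mediation, values below 1.00 point only to potential mediation, the aim is exploratory, and the article says no power was calculated for it. This stands as a limit on the point: nothing here threatens a primary or secondary conclusion. It does not save the cut-off, because an indicator crossed in half of null trials is no help in choosing hypotheses either.

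Four stronger readings are tempting, and the document does not support them.

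- *The trial has no other evidence on activation.* The group effect on activation is a planned secondary outcome. If that effect and regression I both had to be significant alongside a ratio below 1.00, signals without mediation would be 2.4% (a = 0, b = -0.4), 6.5% (a = 0.4, b = 0) and 0.3% (a = b = 0), with 74% detection when a = 0.4 and b = -0.4. The plan does not state that combination, so the criticism is of the unlinked rule.
- *Negative ratios expose a further flaw.* A negative ratio needs ab/c above 1, that is, an indirect effect with the same sign as the total effect and larger than it. That points towards mediation.
- *The lack of an interval is itself an error.* A journal article condenses the full plan, and an interval may be given there. The fault is the cut-off that is written down.
- *The plan will declare mediation with a 50% false-positive rate.* The wording claims only an indication.

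**Conclusion.** The point holds for the rule as stated. With a real BTB effect and no mediation, the ratio falls below 1.00 in about half of trials (49-51% at n = 172), and more participants do not help. With no BTB effect the rate is about 63% for an assumed slope of -0.4 and higher for a steeper one. The result rests on linear models fitted to the same participants and covariates. The value of one half follows from the algebra and varies little with the assumed paths, whereas the detection figures do depend on them. This should be corrected, but it is confined to an exploratory aim.

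**What to change.** Drop the 1.00 cut-off as the indicator of mediation, and in its place:

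1. Regress 4-month activation on group (path a), and 4-month PHQ-9 on group plus activation (path b), using the same participants and covariates in both.
2. Report a x b with a bootstrap 95% confidence interval. Describe the result as consistent with potential mediation only if the interval excludes zero.
3. Keep the ratio of the two treatment coefficients as a description only.
4. State that activation is not randomized and is measured at the same time as 4-month PHQ-9, so an unmeasured common cause can give a non-zero a x b. The new rule controls chance signals, not this bias.
5. Apply the same change to the 8-month repeat, and note there that the wait-list arm has by then been offered BTB.

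The cost is one extra regression, a bootstrap and a few lines of text. The variables are already collected, and the article says trial procedures are still in progress. The downside is that weak true mediation will be flagged less often: about 73-74% against 99% with assumed paths of 0.4 and -0.4.

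### The 8-month repeat of the mediation ratio divides by a group effect that the trial's own hypotheses put near zero

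*Protocol article*

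**What the plan says.** The exploratory part of the Analytic plan sets out three regressions. The first relates 4-month behavioral activation to 4-month PHQ-9. Of the second it says: "The second regression will evaluate the relationship between group assignment (the independent predictor variable) and symptom severity at 4-months". The third adds activation to the second. The strength of mediation is then to be judged as follows: "compute the ratio of the unstandardized betas for treatment assignment (beta from regression III divided by beta from regression II"). The plan attaches this reading to the result: "with values less than 1.00 indicating potential mediation". The next sentence extends this to the later visit: "We will repeat these analyses using 8-month values of the PHQ-9". Only the PHQ-9 time point changes, and no restriction to one arm is given.

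Two other sections bear on that extension. The Wait-list control group section says: "After completion of the 4-month reassessment, participants in this group receive the entire BTB intervention as delivered to the initial treatment group". Under Aims and study hypotheses, the trial expects that "participants in the initial treatment group will maintain reduced symptom presentation from 4 to 8 months" and that "the wait-list control group will show similar reductions in depressive symptoms as the initial treatment group".

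**The concern.** The denominator of the ratio is the total effect of group assignment on PHQ-9. At 4 months this is BTB against no BTB, which is the contrast the trial was designed to show. At 8 months both arms have been offered BTB, and the plan's hypotheses predict that the arms will have converged. The denominator therefore shrinks towards zero exactly when the trial succeeds.

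The mediator adds a second difficulty. The only activation time point named for these regressions is 4 months. In wait-list participants that value was recorded before they received BTB, so it cannot carry the effect of their treatment.

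Behavioral activation is described in the aims as the key active ingredient, and the Analytic plan says the exploratory results are meant to guide refinement of the intervention and its dissemination. An 8-month ratio whose side of 1.00 depends on the chance sign of a residual group difference could misdirect that work.

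**Working it through.** The protocol gives no value for the ratio, so there is no stated figure to reproduce. The check has an algebraic part and a simulation.

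**Algebra.** Write *a* for the group difference in activation, *b* for the slope of PHQ-9 on activation given group, and *T* for the total group effect (the regression II coefficient). In least squares the regression III coefficient equals *T* - *ab*, so

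ratio = (*T* - *ab*) / *T* = 1 - *ab*/*T*.

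The ratio is below 1.00 exactly when the estimates of *ab* and *T* have the same sign. If BTB raises activation (*a* > 0) and activation lowers PHQ-9 (*b* < 0), *ab* is almost always estimated as negative. The rule then reduces to asking whether the estimated 8-month group difference happens to be negative. It says nothing further about activation.

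**Inputs.**
- From the protocol: 208 enrolled, 10% attrition, 172 evaluable in the sample-size calculation, and a 4-month effect of d = 0.40.
- Assumed, because the protocol does not give them: the activation shift and the slope. Two sets were used, (0.4 SD, -0.3) with 188 analysed (208 less about 10%, 94 per arm) and (0.5 SD, -0.4) with 172 analysed (86 per arm).

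**Standard error of *T*.** In the first set the within-arm variance of PHQ-9 is 1 + 0.3² = 1.09, so SE = √1.09 × √(2/94) = 0.152. In the second set the within-arm SD is 1, so SE = √(2/86) = 0.152.

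**Chance of a ratio below 1.00 by hand**, taking it as the chance that *T* is estimated as negative:
- *T* = 0: 50%
- *T* = -0.1: Φ(0.1/0.152) = 74%
- *T* = +0.1: 26%
- *T* = -0.2: Φ(0.2/0.152) = 91%

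**Simulation, 4-month activation as mediator.**

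| True group effect *T* (SD) | n, shift, slope | Central 95% range of ratio | Below 1.00 |
|---|---|---|---|
| 8 months, 0 | 188, 0.4, -0.3 | about -11 to +13 (negative in 29%) | 50% |
| 8 months, 0 | 172, 0.5, -0.4 | about -20 to +20 (negative in 42%) | 50% |
| 8 months, 0 | 172, 0.5, -0.2 | -10.3 to +11.4 | about 50% |
| 8 months, -0.10 | 172, 0.5, -0.4 | -15.9 to +16.8 | 74% |
| 8 months, -0.20 | 172, 0.5, -0.4 | -7.3 to +7.4 | 91% |
| 4 months, -0.40 | 188, 0.4, -0.3 | about 0.00 to 0.93 | 99% |
| 4 months, -0.40 | 172, 0.5, -0.4 | -0.53 to 0.81 | 99.5% |

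The tails of so unstable a ratio move by a unit or more between simulation runs, so the extreme limits are approximate. In the first set, moving the 8-month difference from -0.1 to +0.1 SD moves the chance of a ratio below 1.00 from 74% to 26%, although the activation pathway is unchanged.

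**Simulation, 8-month activation as mediator.** If the arms have converged on activation as well (*a* = 0, *T* = 0), nothing is mediated. The range is then about -2.8 to +4.2 with 188 analysed, and -3.7 to +5.3 with 172. The ratio is below 1.00 in 59% and 63% of trials respectively.

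**The case against.** The strongest reply has four parts.

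*Similar is not equal.* The hypothesis is worded as a within-group comparison, the early arm may improve further after month 4, and the earlier trials cited for the sample size show effects that change with time. A residual early-versus-delayed difference is compatible with the plan. This stands: the denominator is expected near zero, not exactly zero. It does not rescue the ratio. A residual of -0.20 SD still leaves a range of about -7 to +7 in one set of assumptions. In the other it leaves about -4 to +5. The ratio is then usually below 1.00, but only because the group difference is usually negative. The contrast is also still early against delayed BTB, which is not the effect whose mechanism is in question.

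*The mediator's time point is not settled.* The 4-month value is named in the first regression, and the third gives no time. Activation is also an 8-month outcome. This stands too, and under the 8-month reading the range is much narrower. The argument that activation predates treatment in the wait-list arm applies only to the 4-month reading. The ratio is uninformative under either.

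*The inputs are assumed.* The shift and slope are not in the protocol, and a zero total effect alongside a non-zero activation path requires a direct effect that cancels it. The ranges are illustrative. The identity ratio = 1 - *ab*/*T*, and the instability as *T* nears zero, do not depend on those values.

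*It is exploratory.* No decision rule or error rate rests on it, and the plan speaks only of potential mediation. This limits the consequence. It does not make the statistic valid.

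**Conclusion.** The concern holds. As written, the 8-month repeat computes a ratio that either has a near-zero denominator, if the trial's hypotheses are right, or refers to a different contrast, if they are wrong. With a zero 8-month difference and 4-month activation as mediator, its central 95% range is roughly ±10 to ±20, depending on the assumed activation effects, and it falls below 1.00 in about half of trials. With 8-month activation and converged arms it falls below 1.00 in about 60% although nothing is mediated.

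Reading the repeat as confined to the treated arm is not possible, because regressions II and III need group assignment as predictor. Elsewhere the article respects the limit. It places the true two-group comparison at 4 months, keeps the retention analysis within the treatment group, and limits the 8-month cost-effectiveness analysis to those treated first.

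The primary analysis and the 4-month mediation analysis are not touched by this point. It is a moderate-priority correction to a stated exploratory analysis.

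**What to change.** Delete the sentence that repeats the analyses with 8-month PHQ-9, and state that regressions II and III and their ratio apply to the 4-month randomised contrast only.

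If later information is wanted, use the initial treatment arm alone. Regress 8-month PHQ-9 on 4-month activation, adjusting for baseline PHQ-9, baseline activation and 4-month PHQ-9, and report the result as a non-randomised association, not as mediation. This keeps activation earlier in time than the outcome.

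The change costs only wording in the analysis plan and needs no new data. The one loss is that no 8-month mediation figure will be reported.
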